## Methods

### Objectives and hypotheses

In 2011, the Co-Venture Trial was funded by the Canadian Institutes of Health Research (CIHR) to test the 4-year impact of the Preventure programme on delaying early onset drinking and binge drinking in students as well as long-term addiction outcomes. A subsequent CIHR grant was awarded for the Neuroventure study, allowing us to add longitudinal neuroimaging measures to test the following objectives/hypotheses:Compare high-risk (IMP and SS) and low-risk youth on measures of brain structure and function to quantify neurocognitive endophenotypes of these two risk profiles prior to exposure to alcohol in adolescence. We expect to observe impaired fronto-striatal connectivity and function during response inhibition in IMP as well as altered function of frontal and sub-cortical regions (i.e., basal ganglia and ventral striatum) during reward anticipation in SS.Measure the correlates of adolescent drinking and binge drinking on the development of brain structure and function in adolescence, controlling for baseline differences in personality, cognitive profiles, and neural measures that are implicated in the predisposition to early onset alcohol misuse. By comparing youth who take up drinking to those who do not (regardless of intervention status), we will test the extent to which binge drinking trajectories are associated with delayed or altered development of fronto-striatal and fronto-limbic networks that mediate response inhibition and anticipation of reward/punishment. Three hypotheses will be examined. i) Global effects: abnormalities will be observed systematically across all measures of brain function and structure, ii) Developmental specificity: alcohol-induced abnormalities will be specific to regions and cognitive processes that are maturing in adolescence, and iii) Interaction effect: alcohol will exacerbate the abnormalities shown to characterize each high-risk group at baseline.Test causal hypotheses by testing whether delaying drinking (through the Preventure Programme) can produce observable protective effects on structural and functional brain development. By comparing high-risk youth who received intervention to those who did not, we will estimate an intervention effect on structural and functional brain outcomes, which again might be expressed globally across the brain, or more specifically in those areas developing during adolescence or most abnormal in high-risk groups (as revealed in objective 1).

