### Neuroventure: neuroimaging add-on study

#### Participants

Neuroventure will focus on high-risk students with SS and IMP personality profiles as they contribute most to the prediction of early onset substance-related behaviors in adolescence [42]. Thus, a subsample from the Co-Venture Trial of 60 high SS (30 of whom will receive the intervention), 60 high IMP (30 of whom will receive the intervention) and 30 low-risk (low SS and low IMP will not be invited to participate in the interventions) Grade 7 students (50% girls) will be invited to participate in this neuroimaging study (Please refer to Fig. 1 for the consort diagram and to Fig. 2 for the actual recruitment data). An independent informed consent from parents and adolescents will be obtained for the present study. Exclusion criteria will include major neuro-developmental disorders (e.g., autism), uncorrectable visual impairment or hearing deficits, severe mental health problems (e.g., schizophrenia, bipolar disorder), uninterruptable central nervous system medication, and any magnetic resonance imaging (MRI) contraindications (e.g., pregnancy, braces, etc.).

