#### Sample size justification

An estimated 125 subjects in total will be required to identify a moderate effect of personality group (high SS, high IMP, low-risk) on brain measures, prior to the initiation of alcohol use, with 4 covariates, critical F(2, 118) = 3.07, *p* = 0.05, 85% power. Another 25 participants will be added to the sample to allow for attrition (15% over 4 years, based on previous studies). This sample size will provide 90% power to assess moderate group differences in developmental trajectories of alcohol use (group by time interactions) within a longitudinal design with 3 repeated assessments and corrections for multiple testing, critical F(4240) = 3.40, *p* = 0.001. The current study will be sufficiently powered to detect two-year changes on functional and structural data, considering numerous previous studies of similar size showing moderate (*r* = .30) age-related activation in cortical and subcortical regions of the brain when performing fMRI tasks tapping attention and higher cognitive abilities [10]. Similar power is required to test the effects of intervention.

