The main strengths of the study are that (i) the selection, intervention and measurement models are highly time-sensitive, capturing critical periods (12–14 and 14–16 years of age) when personality endophenotypes translate to risk for binge drinking and when early intervention can produce preventative effects. Furthermore, (ii) this critical period appears to overlap with the age at which drinking onset is highly related to future drinking [73], and when important brain maturation occurs [10]. In addition, (iii) this research design is highly powered as our screening procedure, which is largely based on personality assessment at 12–13 years of age, identifies individuals, SS and IMP youth, for whom binge drinking is almost certain to develop within the next 12 months. Our previous research has shown that at 13 years of age, high SS and IMP adolescents have normal rates of drinking and binge drinking (around 40%), but experience a rapid rate of onset of binge drinking between 14 and 15 years of age, with approximately 95% reporting binge drinking at 15 years of age [34]. We will also be able to (iv) test critical questions on the causal pathway from premorbid risk markers to early onset drinking, disruptions in brain function and, in turn, addiction outcomes. Finally, by being embedded into a larger population-based 5-year longitudinal randomized controlled trial, we will be able to directly (v) test the generalizability of our sample and findings to the general population, which is unique for pediatric neuroimaging studies, which tend to involve highly selective clinical samples or families with high education and socio-economic characteristics.

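### Objective 1 is stated and powered as a comparison before alcohol, but the article's own figure at age 13 is around 40% and no stated rule handles prior drinking in the baseline contrast

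*Protocol article*

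**What the plan says.** Under Objectives and hypotheses, the first aim is to compare high-SS, high-IMP and low-risk youth "to quantify neurocognitive endophenotypes of these two risk profiles prior to exposure to alcohol in adolescence". The Sample size justification repeats the condition. It says "An estimated 125 subjects in total will be required to identify a moderate effect of personality group", that this effect is to be found "prior to the initiation of alcohol use", and it gives "critical F(2, 118) = 3.07" at 85% power with four covariates. A further 25 participants are added, for attrition only.

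The first scan falls in the Grade 7 baseline year (Procedure), and the Discussion puts the personality screening at 12–13 years. The same Discussion paragraph states that at 13 "high SS and IMP adolescents have normal rates of drinking and binge drinking (around 40" per cent), citing the team's previous research.

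The Participants section begins its list with "Exclusion criteria will include major neuro-developmental disorders (e.g., autism") and goes on to sensory, psychiatric, medication and MRI grounds. Alcohol is not among them. The covariates named under Statistical analyses include use of other drugs but not earlier alcohol use. A Timeline Follow-Back interview records alcohol use over six months (Behavioral assessment), but the article does not say that it defines or adjusts the Objective 1 comparison. The one mention of splitting by alcohol exposure, under Statistical analyses, is attached to the intervention comparison over time.

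**The concern.** The study is meant to separate what precedes drinking from what follows it. Objective 1 carries the first half of that claim: a difference seen at baseline is to be read as a pre-existing endophenotype. If some high-risk youths have already been drinking, a baseline difference may partly reflect alcohol, and this contrast cannot tell the two apart.

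The power statement is affected too. It is attached to a pre-alcohol comparison. If only youths who have not drunk can support that claim, fewer than the planned 150 are available for it, and nothing in the sample size was set aside for the loss.

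**Working it through.** **1. Reproduce the stated figure.** Three groups and four covariates give df1 = 2 and df2 = 125 − 3 − 4 = 118. The 5% critical F is 3.073, as printed. The article calls the effect moderate without giving a value, so f is inferred. With λ = f²N and f = 0.30, λ = 0.09 × 125 = 11.25 and power is 85.15%; 125 is the smallest N that reaches 85%. With f = 0.25, power at 125 is 69.5% and 178 would be needed. So f = 0.30 is the value that reproduces the plan.

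**2. How many may be exposed.** The 40% applies to age 13 in earlier research, so the share in this sample is assumed to lie between 10% and 40%. Among 120 high-risk youths that is 0.10 × 120 = 12 to 0.40 × 120 = 48.

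**3. Power of an alcohol-naive comparison.** The baseline scan precedes attrition, so the starting number is 150 (power 91.3% if all are used). With f = 0.30 and df2 = N − 7:

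| Prior use | All groups affected: N | Power | High-risk groups only: N | Power |
|---|---|---|---|---|
| 10% | 135 | 87.9% | 138 | 88.7% |
| 20% | 120 | 83.5% | 126 | 85.5% |
| 30% | 105 | 77.9% | 114 | 81.4% |
| 40% | 90 | 70.7% | 102 | 76.5% |

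For example, at 40%: 0.60 × 150 = 90, or 0.60 × 120 + 30 = 102. The stated 85% roughly holds up to about 20% prior use and not beyond. At f = 0.25 the two 40% entries become 53.9% and 59.7%.

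These figures take f as given for the groups as allocated. If f = 0.30 is instead defined for equal groups and the low-risk group alone differs, the difference is 0.30/√(2/9) = 0.636 SD. The 60:60:30 split then gives 79.5% at 150, 73.5% at 36:36:30 and 55.5% at 36:36:18.

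**4. Bias in the high- versus low-risk contrast.** Let p be the share exposed and d the alcohol shift in SD units, for high-risk (H) and low-risk (L) youths. Then bias = p_H·d_H − p_L·d_L. The documents give no d, so these values are illustrations only:

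- Same effect, d = 0.5, p_H = 0.40: 0.20 SD if p_L = 0; 0.10 SD if p_L = 0.20; 0 if p_L = 0.40.
- Same effect, d = 0.2, p_H = 0.40: 0.08, 0.04 and 0 SD.
- Same effect, d = 0.5, p_H = 0.10, p_L = 0: 0.05 SD.
- Equal exposure of 0.40, d_H = 0.5, d_L = 0.2: 0.40 × (0.5 − 0.2) = 0.12 SD.

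The bias is zero when exposure and effect are equal across risk groups. The scenario with the lowest power in the table (N = 90) has equal exposure, so it carries no bias unless alcohol acts more strongly in high-risk youths.

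**The case against.** The 40% comes from other cohorts at 13, while screening here is at 12–13. The article does not say whether it means lifetime or recent use, or how one figure covers both drinking and binge drinking. The same paragraph places the steep rise between 14 and 15, after the first scan. It also calls the 40% rate normal, which suggests similar exposure in low-risk youths and hence possibly no bias. All of this stands. It is why the share is treated as an assumed range and why bias is described as conditional.

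The exclusion and covariate lists are worded as open lists, the two flow figures are not shown, and analysis sets are commonly left to a fuller document. A reader might infer that every enrolled youth enters the baseline analysis, or that prior use is ignored throughout. The article says neither: exposure appears in the intervention comparison, and drinking defines the Objective 2 groups. What can be said is only that no rule is stated for the Objective 1 contrast.

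A reader might also infer that Objective 2 relies on a pre-alcohol baseline scan. Its text does not say so; it adjusts for baseline personality, cognitive and neural measures.

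Hypothesis (iii), that alcohol worsens the abnormalities of high-risk youths, is one of three to be tested. It makes a stronger effect in those groups a live possibility, not an established fact.

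Finally, restricting to youths who have not drunk may select atypical members of the risk groups, so there is no clear case for making that subset the primary analysis.

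None of this removes the conflict between a comparison described as preceding alcohol and a reported rate of around 40% close to the baseline age.

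**Conclusion.** The article contradicts itself on the premise of Objective 1, and this should be fixed. Confidence is moderate, because the exposure at baseline is unknown and an unstated rule cannot be ruled out.

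The reading that 48 high-risk youths have already drunk, or that the baseline contrast is biased by a known amount, is not supported. Forty-eight is the count at the top of the assumed range, and the bias could be zero.

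What is supported is narrower. The pre-alcohol claim is not secured by anything stated, and the 85% power need not apply to it. For a naive subset of the planned 150, power runs from about 88% (10% prior use) to 71–77% (40%). This rests on the inferred f = 0.30 and on f being unaffected by the unequal group sizes.

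**What to change.** - Classify alcohol use before the first scan from the baseline Timeline Follow-Back and any Co-Venture baseline substance-use data. The interview alone covers six months and cannot establish that a youth has never drunk.
- Include prior use and its interaction with risk group in the Objective 1 model. This costs three degrees of freedom (one for prior use, two for the interaction).
- Report the alcohol-naive subset alongside, limit the pre-alcohol claim to it, and state its power over the range above. Otherwise, drop the pre-alcohol wording from the objective and the sample size text.
- In Objective 2, code youths who were already drinking at baseline, so that a scan taken after exposure is not treated in the same way as one taken before.

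The Timeline Follow-Back is already planned, so no new measure is required. The cost is a little more analysis and a less favourable stated power for the pre-alcohol claim.

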## Abbreviations

BART: Balloon Analogue Risk Task
BOLD: Blood oxygenation level dependent
CIHR: Canadian Institutes of Health Research
CMS: Children’s memory scale
DWI: Diffusion weighted imaging
EPI: Echo planar imaging
FA: Fractional anisotropy
fMRI: Functional magnetic resonance imaging
IMP: Impulsivity
MIDT: Monetary Incentive Delay Task
MRI: Magnetic resonance imaging
ROI: Region of interest
SOPT: Self-Ordered Pointing Test
SS: Sensation-seeking
SURPS: Substance Use Risk Profile Scale
TE: Echo time
TR: Repetition time
VBM: Voxel based morphometry
